### Other outcomes

Sociodemographic information on age, gender, language skills, partnership, number of children, level of education, and professional qualifications are collected by self- developed questions.

Therapeutic treatments during the rehabilitation program are recorded according to the classification of therapeutic services [43]. We derive these treatments and their duration in minutes or hours from the standardized medical discharge reports [42].

FESS: Pain Self-Efficacy Questionnaire (German: Fragebogen zur Erfassung der schmerzspezifischen Selbstwirksamkeit), COPSOQ: Copenhagen Psychosocial Questionnaire, IRES-24: Indicators of Rehabilitation Status (German: Indikatoren des Rehastatus), FESV: Questionnaire for the Assessment of Pain Processing (German: Fragebogen zur Erfassung der Schmerzverarbeitung), eHEALS: eHealth Literacy Scale, ZUF-8: Client Satisfaction Questionnaire (German: Fragebogen zur Messung der Patientenzufriedenheit), SUS: System Usability Scale. All instruments except the FESV were freely available and/or licenced with permission to use, share, adapt and reproduce. The FESV has to be purchased. Our self-developed items and questions can be used, shared, adapted and reproduced. Participant timeline.

A timeline of enrollment, intervention, and assessments is shown in Table 4.

**Table 4 Tab4:** Participant timeline

*Timepoint*	*Pre-intervention*	*Beginning of intervention*	*End of intervention*	*3-month follow-up*	*12-month follow-up*
**Enrollment**					
Information and informed consent	x				
Randomization and allocation	x				
**Intervention**					
Rehabilitation		x	x		
**Assessments**					
Questionnaire		x	x	x	x
Standardized discharge report			x		
Guided interview			x	x	

### Sample size

A difference of four points for pain self-efficacy [25] was determined as the minimum relevant difference between the intervention and control group. The minimum required sample size for our non-inferiority analysis is 242 participants (one-sided error: 5%, power: 90%) to perform an intention-to-treat analysis after multiple imputation. The standard deviation for our sample size calculation was taken from the randomized controlled trial on the effectiveness of the study by Mangels et al. [46]. We are planning to recruit 320 participants from eight outpatient rehabilitation centers (intervention group: *n* = 160; control group: *n* = 160), which result in 20 participants for both arms of the study within each outpatient rehabilitation center. The sample size is sufficient for a secondary analysis including only patients with complete follow-up. The anticipated flow of participants is shown in Fig. 1.

**Fig. 1 Fig1:**
[figure not shown]
Flow of participants

### Recruitment

The recruitment is conducted in eight different outpatient rehabilitation centers. Study assistants recruit new study participants as follows: First, every new arriving patient is informed orally about the study. Second, eligible and interested study participants are handed a patient information leaflet as well as a consent form. Third, potential study participants are asked for their informed and written consent. The patient information letter and the consent form are accessible as additional file 3 and 4. Lastly, after informed consent, the study participant is randomly assigned to the intervention or control group.

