### Allocation

Randomized allocation is done in a one-to-one ratio. The principal investigator at the University of Lübeck generated all randomization sequences using Stata 16.1 (StataCorp, College Station, Texas, USA). For each outpatient rehabilitation center, 40 assignments were randomly combined in blocks of four and eight, and the University of Lübeck provided the rehabilitation centers with 40 identical, non-transparent, sealed envelopes numbered from 1 to 40. The envelopes contain the information about the group allocation and personal identification number. Before opening the envelopes, the content of the envelopes was unknown to everyone, excluding the principal investigator. The envelopes are handed out consecutively from 1 upwards to the participants, after informed consent was given. A study assistant in each outpatient rehabilitation center enrolls the participants and registers the group allocation in the study list (Microsoft Excel) using the personal identification number. Due to the nature of the intervention, there is no blinding in the study.

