### Data collection

Quantitative data are collected with questionnaires and standardized rehabilitation discharge reports. Qualitative data are collected with interviews by phone. An overview of the collected data and measurement time points is shown in Table 4. A description of the included assessments is given above.

The first and second questionnaires, together with a prepaid and preaddressed envelope to the University of Lübeck, are given to the participant by a study assistant in the outpatient rehabilitation center. Questionnaires are marked with the personal identification number of the participant only. The participant completes the questionnaires, puts them in the envelope and returns the sealed envelope to the study assistant. The study assistant sends the envelope to the University of Lübeck. For the third and fourth questionnaires, participants are contacted by mail through the University of Lübeck directly. Participants send the completed questionnaires back by again using a prepaid and preaddressed envelope. Patients whose follow-up questionnaires have not been received at the University of Lübeck two weeks after completion are reminded once by mail with new questionnaires, as well as a prepaid and preaddressed envelope to the University of Lübeck. The standardized medical discharge reports are sent to the University of Lübeck after the recruitment phase is over and contain all documented therapeutic treatments during rehabilitation. Researchers from the University of Lübeck conduct the guided interviews between the second and third measurement time points. Participants can withdraw their consent at any time and all collected data will be deleted accordingly.

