### Statistical analysis

We analyze the short-term effects (end of rehabilitation and 3-months follow-up) and long-term effects (12-months follow-up) to show non-inferiority of the hybrid rehabilitation program. The results of the short- and long-term effects will be published separately.

To test the primary hypothesis of non-inferiority, the confidence interval method is applied [47, 48]. We determined -4 points as the non-inferiority margin. Four points are slightly below the smallest clinically important difference (5.5 to 8.5 points) reported in a recent systematic review on pain self-efficacy in patients with low back pain [49]. We assume non-inferiority of the hybrid rehabilitation if the lower boundary of the one-sided 95% confidence interval (CI) exceeds -4 points.

The estimate of the treatment effect is adjusted for the baseline scores of the dependent variable, as well as for the treatment center (outpatient rehabilitation center). To estimate group differences for continuous and binary outcome variables, linear or logistic regression is calculated. Regression coefficients or odds ratios and their 95% CI are determined. Confidence intervals are two-sided for all secondary outcomes.

Age, sex, level of education, electronic health literacy, and motivational self-efficacy are considered as moderators of the treatment effect on our primary outcome variable. The interaction effects are assessed through p-values. All secondary outcome variables are tested on superiority of the intervention group, and we present p-values. We test superiority to identify potential group differences that, in the case of non-inferiority, can be used to formulate a preference for one of the two treatments [50].

In order to perform an intention-to-treat analysis, missing values are imputed by multiple imputation using 20 independent data sets [51, 52]. The parameter estimates are combined according to Rubin’s rules [53].

A sensitivity analysis also calculates unadjusted estimates for the intention-to-treat analysis. An additional sensitivity analysis is conducted as complete case analysis. Like in the primary analysis, we adjust for the baseline scores of the dependent variable and for the treatment center. We also conduct a per-protocol analysis, including only individuals in both groups who participated in six of the seven back school modules.

Withdrawal from consent leads to deletion of the participant’s data.

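### The article indicates that baseline pain self-efficacy is recorded after the arm is known in an unblinded trial, so the primary model may adjust for a covariate that disclosure has shifted

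*Protocol article*

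**What the plan says.** Four parts of the protocol article bear on the order of events.

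- **Recruitment.** The steps are oral information, leaflet and consent form, written consent, and then: "Lastly, after informed consent, the study participant is randomly assigned to the intervention or control group". No questionnaire is mentioned before assignment.
- **Table 4 (participant timeline).** The row "Randomization and allocation" is marked under pre-intervention. The row "Questionnaire" is empty in that column and first marked under the beginning of the intervention.
- **Allocation and Data collection.** "The envelopes are handed out consecutively from 1 upwards to the participants, after informed consent was given". Also: "The envelopes contain the information about the group allocation and personal identification number". On the forms: "Questionnaires are marked with the personal identification number of the participant only". The envelopes also carry a running number, 1 to 40 in each center.
- **Blinding.** "Due to the nature of the intervention, there is no blinding in the study".

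On the use of the baseline score, the Statistical analysis section says: "The estimate of the treatment effect is adjusted for the baseline scores of the dependent variable". Treatment center is the other covariate. Electronic health literacy and motivational self-efficacy are two of the five planned moderators, and Table 3 shows both first measured at the start of rehabilitation, on the same questionnaire. An unadjusted intention-to-treat estimate is planned as a sensitivity analysis.

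**The concern.** Adjusting for a baseline score is safe because randomization makes its expected value equal in the two arms. That holds only if the score is fixed before anyone can react to the allocation. Here the score is a self-rating of how confident the patient is of managing activities despite pain, and the article points to its being given once the patient knows whether the back school will be online or face to face. If that knowledge moves the rating differently in the two arms, the model treats the difference as a pre-existing imbalance and corrects for it, although there was none.

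The result at stake is the lower confidence limit for the primary outcome, which is compared with a margin of -4 points. In a non-inferiority trial an error in favour of the new arm is the costly one, because it can produce a false claim. The two self-rated moderators are exposed in the same way.

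**Working it through.** **1. Is the order supported?** Recruitment puts assignment straight after consent, with no questionnaire before it. Table 4 independently puts the first questionnaire one column after allocation. The identification number marked on the form becomes available when the envelope is opened, and opening it also reveals the arm. Nothing in the article says that the form is completed before disclosure. The order is therefore the natural reading, but it is an inference.

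**2. Form of the bias.** With a common slope b on baseline, the adjusted estimate is

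(difference in mean outcome, hybrid minus control) - b × (difference in mean baseline, hybrid minus control).

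If disclosure changes the baseline difference by s, the estimate moves by -b × s. A lower baseline in the online arm (s negative) moves it towards non-inferiority. A higher one moves it away.

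**3. Inputs.** From the article: margin 4, one-sided 5%, power 90%, minimum N 242, planned N 320 (160 per arm). Assumed: the SD, the slope, the baseline-outcome correlation and s.

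The SD is not printed, so the sample size of 242 cannot be checked independently. Solving backwards with 121 per arm:

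SD = 4 × √(121/2) / (1.645 + 1.282) ≈ 10.63.

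An SD of 10.6 returns 2 × (1.645 + 1.282)² × 10.6² / 4² ≈ 120.3, so 121 per arm and 242 in total. I use 10.6.

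**4. Standard error with b = correlation = 0.5.**

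- 160 per arm: 10.6 × √(2/160) × √(1 - 0.25) = 1.026
- 121 per arm: 10.6 × √(2/121) × √(1 - 0.25) = 1.180

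**5. False non-inferiority at a true difference of -4**, that is Φ(-b × s / SE - 1.645):

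| Baseline shift in online arm, s | Bias | 320 analysed | Information of 242 |
|---|---|---|---|
| 0 | 0 | 5% | 5% |
| -1 | +0.5 | 12.3% | 11.1% |
| -2 | +1.0 | 25.1% | 21.3% |
| +1 | -0.5 | 1.6% | not computed |

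For example, with s = -1 and 320 analysed, Φ(0.5/1.026 - 1.645) = Φ(-1.158) = 0.123. With s = +1, Φ(-0.487 - 1.645) = Φ(-2.132) ≈ 0.016.

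**6. Sensitivity to the slope.** With b = correlation between 0.4 and 0.7 and 160 per arm, the error is 7% to 11% at s = -0.5, 10% to 21% at s = -1 and 18% to 50% at s = -2. With s = +2, power at a true difference of 0 falls from 98-99.9% to 90-92%.

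**7. After the change.** If the form is sealed before the envelope is opened, s = 0 by design, the bias is 0 and the error at the margin returns to 5%. The sample size is unaffected.

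**The case against.** The strongest reply is that the order is never stated. Assignment after consent is standard, Table 4 uses broad phases, and a journal article condenses enrolment-day detail. A reader might go further and infer that a form cannot be identified until the arm is known. The documents do not support that: center plus the number on the outside of the envelope could identify a form, and the article does not say that marking precedes completion. This part of the reply stands, so the order should be described as indicated, not established.

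Second, nothing shows that a shift occurs. The FESS asks about activities despite pain, not about the back school. Both arms receive the same seven modules and an individual program at the center, patients consented to either arm, and those without suitable internet, device or camera are excluded. This also stands: a shift is possible, but its size and sign are unknown. A reader might infer from the 12% and 25% that the trial is biased towards non-inferiority. They show one direction only, and the opposite shift makes the test conservative. At b = 0.5 a 0.25-point shift would give only Φ(0.125/1.026 - 1.645), about 6.4%.

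Third, the planned unadjusted estimate does not use the baseline score as a covariate. That is real but partial protection: it is not the primary analysis, and its standard error is larger (10.6 × √(2/160) = 1.185 against 1.026).

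Finally, it is tempting to extend the concern to the multiple imputation. The article does not list the imputation variables, so that would be conjecture.

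The sealed return of the form does not answer the point. It keeps staff from seeing the answers, but the patient still knows the arm.

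**Conclusion.** The concern holds in limited form. The Recruitment, Allocation and Data collection sections and Table 4 together indicate that the first questionnaire follows disclosure of the arm, and nothing in the article contradicts this. Baseline FESS, and the baseline values of electronic health literacy and motivational self-efficacy, are then open to influence from knowledge of the arm.

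The bias in the primary estimate is minus slope times shift. On the stated assumptions, a 1- or 2-point lower baseline in the online arm would raise the 5% error to about 12% or 25% (11% or 21% at the information of 242 participants). A 1-point shift the other way would lower it to about 1.6%. These figures show what would follow from shifts of that size; they do not predict any shift. The order of enrolment-day steps should be changed while recruitment continues, because the remedy is cheap and protects the primary analysis. The design is not invalidated.

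**What to change.** **Remaining participants.** After consent, have the first questionnaire completed and sealed before the allocation envelope is opened. Label it with the center and the number already on the outside of the envelope, and link it to the personal identification number once the envelope is open. Log the order for each participant. Amend Table 4, the Recruitment section and the Data collection sentence on marking to match.

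**Participants already enrolled.** Establish and record which order was followed, compare baseline FESS by arm, and report the already planned unadjusted estimate beside the adjusted one.

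**Cost.** A short delay before allocation, a procedure note to eight centers and one extra linking step. No envelope needs to be opened or reprinted, and margin, model and sample size stay as they are. The main drawback is two baseline procedures within one trial, which the log makes visible. If recruitment has since closed, only the second part applies.

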### Allocation

Randomized allocation is done in a one-to-one ratio. The principal investigator at the University of Lübeck generated all randomization sequences using Stata 16.1 (StataCorp, College Station, Texas, USA). For each outpatient rehabilitation center, 40 assignments were randomly combined in blocks of four and eight, and the University of Lübeck provided the rehabilitation centers with 40 identical, non-transparent, sealed envelopes numbered from 1 to 40. The envelopes contain the information about the group allocation and personal identification number. Before opening the envelopes, the content of the envelopes was unknown to everyone, excluding the principal investigator. The envelopes are handed out consecutively from 1 upwards to the participants, after informed consent was given. A study assistant in each outpatient rehabilitation center enrolls the participants and registers the group allocation in the study list (Microsoft Excel) using the personal identification number. Due to the nature of the intervention, there is no blinding in the study.

### Data collection

Quantitative data are collected with questionnaires and standardized rehabilitation discharge reports. Qualitative data are collected with interviews by phone. An overview of the collected data and measurement time points is shown in Table 4. A description of the included assessments is given above.

The first and second questionnaires, together with a prepaid and preaddressed envelope to the University of Lübeck, are given to the participant by a study assistant in the outpatient rehabilitation center. Questionnaires are marked with the personal identification number of the participant only. The participant completes the questionnaires, puts them in the envelope and returns the sealed envelope to the study assistant. The study assistant sends the envelope to the University of Lübeck. For the third and fourth questionnaires, participants are contacted by mail through the University of Lübeck directly. Participants send the completed questionnaires back by again using a prepaid and preaddressed envelope. Patients whose follow-up questionnaires have not been received at the University of Lübeck two weeks after completion are reminded once by mail with new questionnaires, as well as a prepaid and preaddressed envelope to the University of Lübeck. The standardized medical discharge reports are sent to the University of Lübeck after the recruitment phase is over and contain all documented therapeutic treatments during rehabilitation. Researchers from the University of Lübeck conduct the guided interviews between the second and third measurement time points. Participants can withdraw their consent at any time and all collected data will be deleted accordingly.

### Data management

Data from the questionnaires are entered into computers by trained research assistants or researchers from the University of Lübeck using Microsoft Access forms. The Microsoft Access forms contain the exact set of questions and values from the questionnaires. Data entry is done directly after the questionnaires arrive at the University of Lübeck.

Documented in the study list of each outpatient rehabilitation center is whether the first and second questionnaires were given to the participant, the personal identification number, name, surname, year of birth, address, and gender, as well as the start and end date of rehabilitation. The study list is transferred to the University of Lübeck.

In the monitoring list at the University of Lübeck, all study lists are combined and received questionnaires from all participants at all measurement time points are documented. It is also documented whether the third and fourth questionnaires were sent to the participant from the University of Lübeck, and if written consent was received. Additionally, the University of Lübeck uses the monitoring list is to send out reminder letters to the participants in case of missing questionnaires.

### Data monitoring

An external data monitoring committee is not implemented. Short-term and long-term effects are analyzed and published separately. No further interim analyses are planned. No criteria for early study termination have been established.

### Auditing

Every 2 weeks, the status of recruitment, response rates of the questionnaires, other announcements, and current events are discussed through a video conference between the University of Lübeck and the outpatient rehabilitation centers.

### Confidentiality

Every new study participant is entered into the study list at each outpatient rehabilitation center. All documentation is done by study assistants from the outpatient rehabilitation centers. The study list is password protected. This list is stored on a computer at the outpatient rehabilitation center, and only the study assistants have access to it. Every two weeks, the study assistants send an electronic encrypted copy of the study list to the researchers at the University of Lübeck. After the last enrolled participant finishes the second questionnaire, the study assistants delete the study list.

All received study lists from the outpatient rehabilitation centers are incorporated into the monitoring list at the University of Lübeck. Each received study list is deleted immediately at the University of Lübeck after the content is transferred to the monitoring list. The monitoring list is password protected and stored on the computers at the University of Lübeck. Only researchers involved in the study have access to it. The monitoring list itself will be deleted after the third follow-up is complete (anonymization of the data).

The data from all questionnaires are pseudonymized by the personal identification number on the questionnaire. All completed questionnaires are sent to the University of Lübeck. At the University of Lübeck, the questionnaires are stored in folders and locked in lockers that belong to the office rooms of researchers who are involved in the study. The questionnaires are only accessible to researchers who are involved in the study. All questionnaires will be destroyed in accordance with data protection regulations upon completion of the study.

The interviews are recorded and stored on the computers at the University of Lübeck. The files of the audio recordings are password protected and pseudonymized immediately after the interview is finished. Transcripts of the interviews are also pseudonymized. The audio recordings are deleted after the interviews are transcribed.

Medical discharge reports are pseudonymized by the personal identification number and sent electronically to the University of Lübeck by the study assistant at each outpatient rehabilitation center.

All digital data is stored on password protected computers that require authentication of users. The computers are located in the researchers’ office rooms at the University of Lübeck, which are locked when left. Access to the computers can be tracked. Only researchers at the University of Lübeck have access to the digital data. The network in which the computers are integrated is protected against external access and manipulation by a regularly updated firewall system.

Ten years after the end of the study, all digitalized data from the questionnaires will be deleted.

